The Life Gatekeeper Training Program consists of two main packages. The first package comprises eight sessions of video-recorded training (Table 1), including psychoeducational content, animated films, role-playing, and group discussions, with the training concluding with online group supervision by crisis intervention specialists. For instance, when it is time for the group discussion, there will be a prompt in the video indicating, “It’s time for the group discussion.” A timer will be displayed on the screen, and the instructors or core teachers only need to organize the discussion activity. In addition, the following topics are covered within the program (1) the severity of suicide among children and adolescents, and the common feelings of suicidal persons, (2) establishing a correct understanding of suicide, (3a) risk factors associated with suicide, (3b) identifying the warning signs of suicide, (4) the correct way to communicate suicide risk, (5) assessing suicide risk, (6) making a safety plan, (7) teachers communicating with parents about their kids’ suicide risk, psychoeducating parents on how to express support to their kids, and determining subsequent procedures with parents, and (8) any potential barrier that might stop teachers from providing help, and how to overcome it into actual gatekeeping behaviors.

**Table 1 Tab1:** Contents of the Life Gatekeeper Training Program

Section	Theme	Methods of delivery	Length of training
1	The severity of suicide among children and adolescents, and the common feelings of suicidal persons	Video viewing; group discussion	21 min + 07 sec
2	Establishing a correct understanding of suicide	Video viewing; group discussion	22 min + 35 sec
3	Risk factors associated with suicide, identifying the warning signs of suicide	Video viewing; group discussion	22 min + 12 sec
4	The correct way to communicate suicide risk	Video viewing; group discussion; role play	66 min + 48 sec
5	Assessing suicide risk	Video viewing; role play	47 min + 27 sec
6	Making a safety plan	Video viewing; role play	78 min + 58 sec
7	Teachers communicating with parents about their kids’ suicide risk, psychoeducating parents on how to express support to their kids, and determining subsequent procedures with parents	Video viewing; role play	43 min + 13 sec
8	Any potential barrier that might stop teachers from providing help, and how to overcome it into actual gatekeeping behaviors	Video viewing; group discussion	15 min + 40 sec

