### Secondary outcome

#### Gatekeeper behaviors

The study will also measure the gatekeeper behaviors of participants in both the intervention and control groups at 12 months post-intervention. To measure short-term behavioral changes, the intervention group will also report behaviors at the 6-month mark [37, 38]. This measurement will be conducted using four individual questions that have been adjusted from previous studies to enable a rigorous comparison, taking into account the lagging nature of the observation period for behavior changes. Following questions will be asked (1) During the 6 months/12 months after the training, have you identified any students who may be at risk of suicide (or are experiencing psychological distress)? (2) Among these students, how many have you discussed potential suicide risks (or their psychological distress) with? (3) Among these students, how many have you discussed their suicide risk (or their psychological distress) with their parents? (4) Among these students, how many have you referred to mental health professionals or specialist clinics? Percentage scores will be calculated for each intervention method by comparing the number of students they intervened with to the number of students they identified. These scores will range between 0 and 100%, with a higher percentage indicating a higher frequency of gatekeeper behaviors.

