## Discussion

### Strengths of the study

According to our hypothesis, the Life Gatekeeper Training Program for teachers will lessen the suicide stigma while enhancing their knowledge, skills, and willingness to intervene as gatekeepers, leading to increased actual gatekeeper conducts.

To the best of our knowledge, this is the first RCT study to examine a localized gatekeeper program’s effectiveness, including video-delivered components for primary and secondary school teachers. The program is practical due to its strong emphasis on skill acquisition and practice. It is also instantly accessible to participants as all video clips and workbooks can be retrieved through an online platform anytime and anywhere. Along with advancing the field of suicide prevention and intervention study in China, the proposed program will produce valuable and meaningful evidence-based practice and policy benefits for pertinent stakeholders. Ultimately, it could potentially establish a multi-level suicide prevention system that consists of schools, families, and professional psychological institutions, thereby better safeguarding children and adolescents from suicide.

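### The gatekeeper-behaviour score divides by the number of students identified, which training is meant to raise, so it is not a frequency and its 12-month comparison between arms is not protected by randomisation.

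*Protocol article*

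**What the plan says.** The protocol article names gatekeeper behaviour as its only secondary outcome (Table 2). Under Gatekeeper behaviors it says: "The study will also measure the gatekeeper behaviors of participants in both the intervention and control groups at 12 months post-intervention". The intervention arm also reports at 6 months.

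Four questions are asked. The first is whether the teacher has recognised anyone: "have you identified any students who may be at risk of suicide (or are experiencing psychological distress". The other three ask for numbers among those students: how many the teacher talked with, how many had the matter raised with their parents, and how many were referred, for example "Among these students, how many have you referred to mental health professionals or specialist clinics".

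A percentage is then formed for each type of act "by comparing the number of students they intervened with to the number of students they identified". The stated reading is: "These scores will range between 0 and 100%, with a higher percentage indicating a higher frequency of gatekeeper behaviors".

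Two other places bear on this. The Introduction describes gatekeeper training as giving lay people the skill to identify people at risk, and Intervention program lists topic "3b) identifying the warning signs of suicide". Strengths of the study states the hypothesis that the programme acts on attitudes and skills, "leading to increased actual gatekeeper conducts".

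**The concern.** The denominator is reported after randomisation and is a direct target of the training. Three things follow.

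- **The score does not measure what it is said to measure.** It gives the share of recognised students on whom the teacher acted, not how much the teacher did. A teacher who recognises more students, including less obvious cases, can do more and score lower.
- **The comparison between arms is not protected by randomisation.** If training works, the set of recognised students, and the set of teachers with at least one, differ between arms because of the training.
- **The score has no value at zero identified.** Leaving those teachers out compares groups selected by training. Coding them 0 merges teachers who recognised nobody with teachers who recognised someone and did nothing.

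At stake is the trial's only behavioural outcome, and with it the hypothesis that training increases gatekeeper conduct. A flat or lower percentage could be read as failure when more students had been helped.

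**Working it through.** **Figures in the plan.** The article gives no expected value, power or sample size for the behaviour score, so there is no figure to reproduce on this point. The overall sample size does reproduce: 42 schools × 30 teachers = 1,260 per arm, and 1,260 / (1 − 0.30) = 1,800 recruited. The 1,260 is used below only to give scale.

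**Step 1: the stated reading, with no assumed rates.** Score = students acted on / students identified. One of 1 gives 100%; 8 of 10 gives 80%. The second teacher helped eight times as many students and scores lower, so a higher percentage need not mean a higher frequency.

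**Step 2: when score and amount of help diverge.** Let m be the mean number identified per teacher and p the share acted on (0 = control, 1 = intervention). Students helped per teacher = m × p. If identified numbers are Poisson and each student is acted on with probability p, the mean score among teachers with at least one identified is p. So:

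- the score falls when p1 < p0;
- the number helped rises when p1/p0 > m0/m1.

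Both hold together whenever m0/m1 < p1/p0 < 1. If identification doubles, that means any p1 between half of p0 and p0.

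**Step 3: illustrations.** All rates are assumptions. The fraction of teachers with a defined score is 1 − exp(−m). With non-identifiers coded 0, the mean score is p × (1 − exp(−m)). Each cell shows control → intervention.

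| Identified per teacher | Share acted on = score among identifiers | Helped per teacher | Score, non-identifiers coded 0 | Teachers with a score, of 1,260 |
|---|---|---|---|---|
| 0.5 → 1.0 | 60% → 50% | 0.30 → 0.50 | 24% → 32% | 496 → 796 |
| 0.3 → 0.6 | 80% → 50% | 0.24 → 0.30 | 21% → 23% | 327 → 568 |
| 0.3 → 0.6 | 60% → 60% | 0.18 → 0.36 | 16% → 27% | 327 → 568 |
| 1.0 → 2.0 | 60% → 40% | 0.60 → 0.80 | 38% → 35% | 796 → 1,089 |

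The first row arises, for example, if training adds 0.5 students per teacher who are acted on 40% of the time: (0.5 × 0.6 + 0.5 × 0.4) / 1.0 = 50%. Adding the same 0.5 students to control means of 0.25 and 1.0 gives (0.15 + 0.20) / 0.75 = 46.7% and (0.60 + 0.20) / 1.5 = 53.3%. The score falls in each case, by differing amounts.

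**Step 4: how many teachers have no score.** exp(−m) at m = 0.3, 0.5 and 1.0 is 74%, 61% and 37%. If training raises m, this share differs between arms.

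**The case against.** **Teachers with nobody identified need not be lost.** A reader might infer that the plan drops them. The article does not say so; it gives no rule for zero over zero, and an analysis plan not shown here may supply one. Coding them 0 fits the stated range and restores the direction in the first two rows of the table. This stands. It is not a general cure: in the last row the zero-coded score falls from 38% to 35% while students helped per teacher rise from 0.60 to 0.80.

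**The score need not go the wrong way.** A reader might infer that it will show harm. The documents give no rates and do not support that. Training may also raise action on cases that would have been noticed anyway: Sections 4 to 7 in Table 1 take about 236 of 318 minutes, against about 22 for Section 3, on risk factors and warning signs. If action on the original 0.5 students rose from 60% to 80%, the score would be (0.8 + 0.4) / 2 = 60%, with no fall. Students helped would still double from 0.30 to 0.60 (0.5 × 0.8 + 0.5 × 0.4), and the score would miss it.

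**Identification is not excluded from reporting.** It is the first of the four questions. What the article lacks is a defined score for it. Statistical analysis also names a model only for the primary outcomes, so no specific test of the percentages is fixed. The comparison between arms is implied by collecting the outcome in both arms at 12 months.

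**Counts have weaknesses too.** Teachers are unblinded and report on themselves, and the first question also covers psychological distress, so a count can reward over-labelling. This stands, but the percentages rest on the same answers. Follow-through among identified students is a legitimate descriptive quantity.

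**Conclusion.** The point holds. The definition and its reading are both fixed in the article, and an analysis plan that kept them would inherit the fault. Two conclusions need no assumed rates: the percentage is a conditional proportion and not a frequency, and its denominator is a post-randomisation variable that the training is designed to change.

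The size of any distortion cannot be fixed from the documents. With the assumed rates above, students helped per teacher rise by between 25% (0.24 to 0.30) and 100% (0.18 to 0.36), while the score among identifiers is flat or falls by 10 to 30 points. These figures rest on Poisson counts and chosen shares, and they show what can happen rather than what will.

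This should be fixed because it is the trial's only secondary outcome and its only measure of behaviour. It does not touch the four primary scales or the stated sample size.

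**What to change.** - Make the 12-month comparison between arms on counts per teacher: students talked with, students whose parents were contacted, and students referred (questions 2 to 4). Include all teachers, counting zero for those who identified nobody, and allow for clustering by school.
- Add the number of students identified as an outcome where question 1 is answered as a number. The plan's own denominator already needs that number, although the question as printed asks only whether any student was identified. Where no number was collected, compare any versus none identified.
- Keep the percentages as a description among teachers who identified at least one student.
- Delete the statement that a higher percentage means a higher frequency.

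**Cost.** Questions 2 to 4 already ask for numbers, so most of this is a change to the outcome definition and analysis text. The exception is question 1: if it was fielded as yes/no, the number identified can be collected only in a survey round not yet completed. Trial status places the end of the final follow-up at March 2024. Counts will be skewed and need robust standard errors or a negative-binomial model. They remain unblinded self-reports, as the percentages are.

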### Sample size calculation

Since the current study is designed to be a clustered randomization study, the sample size calculation is based on the number of clusters and the between-cluster coefficient of variation. Sample size calculation was conducted through the cpa.count function in “clusterPower” package in R. The cpa.count is a tool for computing the power, number of clusters needed, number of subjects per cluster needed, or other key parameters for a simple parallel cluster randomized trial with a count outcome [39]. The between-cluster coefficient of variation for the current study is identified as 0.01 based on the reference number defined at “carriage outcomes at 12 months in rural area” [40]. Since we aimed to capture small changes in the outcomes measure, a detectable effect size was set as *r* = 0.1 for power analysis. The number of schools fulfilling inclusion criteria in the local area was 84, which means each group will involve 42 clusters. With a power of 0.85 and alpha=0.05, the mean number of participants calculated for each cluster (school) is 30. A final sample in each group should thus achieve 1260. To account for a withdraw rate of 30%, we will recruit 1800 participants for each group. 

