#### Perceived competence, and willingness to intervene against suicide questionnaire

The Chinese version of the Willingness to Intervene Against Suicide Questionnaire (WIS), will be used to measure participants’ perceived competence and willingness to intervene with students with suicidal risk [35]. The WIS, developed through three studies involving American college students, consists of four subscales. The current study will use the perceived behavioral control subscale to measure participants’ perceived competence to intervene and use the willingness to intervene subscale to measure participants’ willingness to intervene with students with suicidal risks. The perceived behavioral control subscale and the willingness to intervene subscale have 20 and 22 items respectively, capturing a range of methods of intervening with students with suicidal risks. Participants will use a 5-point Likert scale to indicate whether they feel confident or are willing to intervene with a suicidal student through different methods in the perceived behavioral control subscale and the willingness to intervene subscale, respectively. The WIS showed good psychometric properties as a measurement capturing one’s perceived competence and willingness to intervene with a student with suicidal risk [36]. The Chinese version was translated and reviewed by two researchers with previous experience in suicide research who are fluent in both Chinese and English. The total score is the sum of each item for both subscales, with higher scores indicating greater perceived competence and willingness to intervene.

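### The stated 85% power rests on a count-outcome tool, a clustering value from carriage outcomes and an undefined effect r = 0.1, so it is not a demonstrated property of this design for its four primary scores

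*Protocol article*

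**What the plan says.** All the sizing inputs are in the section Sample size calculation of the protocol article.

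- **Tool.** The calculation uses the cpa.count function of an R package, described there as serving to find power, cluster numbers and "other key parameters for a simple parallel cluster randomized trial with a count outcome".
- **Clustering.** The between-cluster coefficient of variation (CV) "is identified as 0.01 based on the reference number defined at" "carriage outcomes at 12 months in rural area".
- **Effect.** Because small changes are of interest, "a detectable effect size was set as *r* = 0.1 for power analysis". The metric of r is not given.
- **Result.** There are 84 eligible schools, 42 per arm. "With a power of 0.85 and alpha=0.05, the mean number of participants calculated for each cluster (school) is 30". This gives 1260 per arm, raised to 1800 for 30% withdrawal.

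The Primary outcomes section defines what is analysed. The stigma score is the sum of five items rated 1 to 5 (range 5 to 25). The literacy score is the number correct out of 11. Perceived competence and willingness come from 20 and 22 five-point items, scored thus: "The total score is the sum of each item for both subscales". The Statistical analysis section sets a two-sided test, generalised estimating equations with demographic adjustment, and a false discovery rate correction.

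**The concern.** The sizing and the outcomes do not belong together. A count-outcome calculation works on event rates, with a variance tied to the mean. None of the four primary outcomes is an event rate, and no rate is given for either arm. The clustering value describes carriage, and nothing in the text connects it to teachers' attitudes, knowledge or confidence. Without a metric, r = 0.1 could be a correlation, a standardised difference, a rate or a difference in rates.

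Between-school variation is a main driver of power when 84 schools are randomised, so its value needs to fit the outcomes. Readers will use the 85% to judge null or small results on four primary outcomes. If the figure is not a property of the design, that judgement has no basis in either direction.

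**Working it through.** **1. The plan's own totals.** 42 x 30 = 1260 and 1260 / (1 - 0.30) = 1800. Both reproduce.

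**2. The core figure (30 per school at 85%) in a count formula.** The article prints no formula. I assume the usual one for a parallel cluster trial comparing rates r1 and r2:

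power = Phi( sqrt[ (c - 1)(r1 - r2)^2 / ( (r1 + r2)/m + CV^2 (r1^2 + r2^2) ) ] - 1.96 )

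with c = 42, m = 30 and CV = 0.01, all from the article. It needs two rates, and the article gives neither. Solving for 85%:

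| Reading of r = 0.1 | Rates needed for 85% |
|---|---|
| Absolute difference of 0.1 | about 0.63 vs 0.73 |
| 10% relative increase | about 1.54 vs 1.69 |
| Rate in one arm | 0.10 vs about 0.142 |

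So some rate pairs return 85%, but they are not stated and do not resemble the outcomes. The stigma score cannot fall below 5, and the other two Likert sums cannot fall below 20 and 22 if items are coded 1 to 5 (coding assumed). At a mean of 5 the formula gives about 19% power for a difference of 0.1 and over 99% for a 10% change. The first two pairs would mean an average of roughly 0.6 to 1.7 correct answers out of 11 on the literacy score.

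**3. What CV = 0.01 implies.** In this formula, at a common mean mu, clustering adds m x CV^2 x mu = 30 x 0.0001 x mu = 0.003 mu to the variance, relative to the within-school part. That is 0.2% at mu = 0.68, 1.8% at mu = 6 and 21% at mu = 70 (illustrative means). On a scale score, the same CV gives ICC = (0.01 x mean/SD)^2, about 0.001 to 0.004 if mean/SD is 3 to 6 (assumed).

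**4. A calculation that fits score outcomes.** Inputs from the article: 42 schools per arm, 30 analysed per school (1260 per arm), two-sided alpha 0.05. The ICC is not in the document, so it is an assumption shown as a range.

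- Design effect: DE = 1 + ((1 + cv^2)m - 1) x ICC, where cv is the coefficient of variation of school size (0 for equal schools).
- Standard error of d: SE = sqrt(2 x DE / 1260).
- Power: noncentral t with 2 x 42 - 2 = 82 df and noncentrality d/SE.
- If r is a correlation: d = 2r / sqrt(1 - r^2) = 0.2 / sqrt(0.99) = 0.201, taken as 0.2.

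Example, ICC 0.05 and equal schools: DE = 1 + 29 x 0.05 = 2.45; SE = sqrt(2 x 2.45 / 1260) = 0.0624; noncentrality for d = 0.2 is 3.21; power 89%.

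| ICC (equal schools) | DE | Power, d = 0.2 | Power, d = 0.1 | d detectable at 85% |
|---|---|---|---|---|
| 0 | 1.00 | 99.9% | 70% | 0.12 |
| 0.02 | 1.58 | 98% | 50.5% | 0.15 |
| 0.05 | 2.45 | 89% | 35% | 0.19 |
| 0.10 | 3.90 | 71% | 24% | 0.24 |

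With school-size cv 0.6 (assumed), power for d = 0.2 at ICC 0.02 / 0.05 / 0.10 is 96% / 82% / 60%, and the detectable d is 0.16 / 0.21 / 0.27.

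For d = 0.2 and equal schools, power equals 85% at an ICC of about 0.06. For d = 0.1, 85% is not reached with 30 per school at any ICC of zero or more.

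**The case against.** Several points limit how far this goes, and most of them stand.

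- **85% can be reached.** A reader might infer that no reading of the inputs gives 85%. That is too strong. Several rate pairs do, and so does a correlation of 0.1 with an ICC of about 0.06. But those rates and that ICC are not in the article, and an ICC of 0.06 is far above what a CV of 0.01 implies in step 3. The figure is unsupported; it is not shown to be miscalculated.
- **Underpowering is not shown.** A reader might also infer that the trial is too small. The documents do not support this. The low figures need r to mean d = 0.1, and every ICC here is assumed. With d = 0.2, power is 89% or more up to ICC 0.05. These are also single-time-point comparisons: baseline adjustment may raise power, and the false discovery rate correction may lower it.
- **Clustering is not fixed at a 0.2% contribution.** It is tempting to say clustering was ignored. The 0.2% holds only for rates near 0.68; at a mean of 70 the same formula gives 21%. What stands is that the CV comes from an unrelated outcome.
- **The literacy score is a number of correct answers**, so loosely a count. It is bounded at 11, so a variance equal to the mean is not justified, but the mismatch is weaker there than for the Likert sums.
- **A condensed article may leave the rates to the full protocol.** True, and the missing rates alone would not be a finding. The outcome type and the source of the clustering value are stated positively, however, and supplying rates would not make either of them fit.

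**Conclusion.** The point holds as a fault of method and assumptions; the printed arithmetic is right. The article pairs a count-outcome tool, a clustering value from carriage and an effect without a metric with three Likert sums and one bounded number-correct score. The 0.85 therefore does not follow from the stated inputs for these outcomes and is not a demonstrated property of the design.

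Power could lie on either side of 0.85. Over assumed ICCs of 0.02 to 0.10 with equal schools of 30, it runs from about 98% down to 71% if r = 0.1 is a correlation, and from about 50% down to 24% if it is a standardised difference. Those ranges rest on the assumed ICCs, on 1260 analysed per arm and on an unadjusted comparison at one time point. The count-formula results also assume the formula shown, because the article does not print one.

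**What to change.** Keep the existing calculation as the historical record and add a dated restatement that:

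1. uses a continuous-outcome cluster calculation with 42 schools per arm, 30 analysed teachers per school, the design effect 1 + ((1 + cv^2)m - 1) x ICC, and 82 df;
2. defines the effect as a standardised mean difference;
3. takes the ICC and school-size cv from pooled baseline data, or shows ICC 0.02 to 0.10 labelled as an assumption;
4. replaces the 0.85 claim, for each primary outcome, with the resulting power or the difference detectable at 85% power (about d = 0.15 / 0.19 / 0.24 at ICC 0.02 / 0.05 / 0.10 with equal schools);
5. notes that baseline adjustment may raise power and that the false discovery rate correction may lower it.

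The cost is one paragraph. All 84 eligible schools are already used and recruitment has ended, so neither the design nor the recruitment changes. The downside is that the stated figure may become less favourable.

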**Methods:**

Participants will be recruited from eligible primary and secondary schools. Cluster sampling will be used to randomly assign each school to either the intervention group or the control group. The primary outcomes are stigma against suicide, suicide literacy, perceived competence, and willingness to intervene with suicidal individuals, which will be measured using the Stigma of Suicide Scale, the Literacy of Suicide Scale, and the Willingness to Intervene Against Suicide Questionnaire, respectively. Measurements will be taken at four time points, including pre-intervention, immediately after the intervention, 6-month follow-up, and 1-year follow-up.

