### Statistical analysis

All statistical analysis will be conducted through R 4.1.0 Analyses. The primary outcomes will be conducted through generalized estimating equations modeling while controlling for all the demographic information [41]. The generalized model will be conducted to analyze the within-group and between-group differences at each time point for all primary outcomes in head-of-class teachers and education staffs. The same model will be applied to core teachers as a supplementary analysis. A 2-sided significance level will be set, and false discovery rate corrections will be applied to account for the risk of false positive generated by multiple comparisons. Descriptive statistics will be conducted for demographic information and process evaluation questions. Analyses will be conducted after the completion of post-intervention, 6-month follow-up, and 12-month follow-up data collection. Since there are no anticipated problems that are detrimental to the participant, no stopping guidelines are set.

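### The stated power of 0.85 is for one uncorrected test at 0.05; under the planned false discovery rate correction it is an upper bound at 1260 per arm

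*Protocol article*

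**What the plan says.** The Sample size calculation uses a routine for a single count outcome in a parallel cluster trial. The target is stated as "a detectable effect size was set as *r* = 0.1 for power analysis", with 42 schools per arm. The result is given as "With a power of 0.85 and alpha=0.05, the mean number of participants calculated for each cluster (school) is 30", hence 1260 per arm, raised to 1800 for 30% withdrawal. Nothing in that section refers to more than one test.

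The abstract names four primary outcomes: "The primary outcomes are stigma against suicide, suicide literacy, perceived competence, and willingness to intervene with suicidal individuals". It also says: "Measurements will be taken at four time points, including pre-intervention, immediately after the intervention, 6-month follow-up, and 1-year follow-up". The Statistical analysis section will "analyze the within-group and between-group differences at each time point for all primary outcomes in head-of-class teachers and education staffs". It continues with "A 2-sided significance level will be set", without giving the level, and then "false discovery rate corrections will be applied to account for the risk of false positive generated by multiple comparisons". It names no procedure, no error rate and no family of tests, and it singles out no outcome or visit as free of correction.

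**The concern.** The power figure belongs to one test judged at 0.05. The analysis will judge each primary contrast after a correction that, in its usual form, can raise a p-value but never lower it. The 0.85 is thus attached to a test that the analysis section does not plan to report.

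What is at stake is how a null result is read. If one of the four outcomes shows no significant difference, a reader of the Sample size calculation will take that null as coming from a test with an 85% chance of finding the design effect. After correction the chance is lower. It is only slightly lower if the programme moves everything, and clearly lower if it moves one or two outcomes, or if effects fade by 12 months.

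**Working it through.** **Inputs from the article.** Power 0.85; alpha 0.05; 42 schools per arm; mean 30 teachers per school; 30% withdrawal; four primary outcomes; three post-baseline visits; a two-sided test (stated in Statistical analysis, assumed for the sample size).

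**The plan's own figures.** 42 × 30 = 1260 and 1260 / 0.70 = 1800, both as stated. The 30 per school cannot be recomputed, because the routine needs two arm rates and only r = 0.1 is given. The 0.85 is taken at face value from here on.

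**Signal implied by the design.** A two-sided test at 0.05 with power 0.85 has an expected z-statistic of z(0.975) + z(0.85) = 1.960 + 1.036 = 2.996.

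**Strictest thresholds.** Power at level a is Φ(2.996 − z(1 − a/2)), ignoring the negligible opposite tail.

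- a = 0.05: Φ(2.996 − 1.960) = Φ(1.036) = 0.850
- a = 0.05/4 = 0.0125: Φ(2.996 − 2.498) = Φ(0.499) = 0.691
- a = 0.05/12 = 0.00417: Φ(2.996 − 2.865) = Φ(0.131) = 0.552

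The families are assumptions: 4 is the four outcomes at one visit, and 12 is the four outcomes at three post-baseline visits (4 × 3). The levels 0.05/4 and 0.05/12 are where Benjamini-Hochberg starts. Its threshold rises with the number of rejections: with k rejections among m tests it is 0.05 × k/m, so it reaches 0.05 when all m are rejected.

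**Benjamini-Hochberg at 0.05, simulated.** Normal z-statistics with a common correlation of 0, 0.5 or 0.8; mean 2.996 for real effects and 0 otherwise; 2,000,000 sets per case. Average power per real effect:

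| Family | Real effects | Corr. 0 | Corr. 0.5 | Corr. 0.8 |
|---|---|---|---|---|
| 4 | 1 | 0.698 | 0.694 | 0.692 |
| 4 | 2 | 0.759 | 0.752 | 0.747 |
| 4 | 4 | 0.834 | 0.818 | 0.810 |
| 12 | 1 | 0.560 | 0.556 | 0.553 |
| 12 | 6 | 0.747 | 0.725 | 0.716 |
| 12 | 12 | 0.832 | 0.806 | 0.792 |

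Against 0.85, the loss is about 2 to 6 points when every contrast is real, 9 to 13 points when half are, and 15 to 30 points when only one is.

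**Direction.** Benjamini-Hochberg rejects only p-values at or below 0.05 × k/m, with k no larger than m. Every rejection would also have been a rejection at 0.05, so with the sample and effect fixed its power cannot exceed 0.85, whatever the family.

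**The case against.** **Uncorrected per-test power is a common convention.** This is fair, and no arithmetic in the section is wrong. But the article does not say that it follows this convention, and the same article commits to correcting the tests.

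**The correction is adaptive and the authors expect a broad effect.** This stands. Under Strengths of the study, the article hypothesises less stigma together with better knowledge, skills and willingness. If all contrasts move as designed, the loss is only 2 to 6 points. A reader might infer a Bonferroni-size loss and take 0.69 or 0.55 as the trial's power. The document does not support that, because those values require exactly one real effect in the family.

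**The sections do not fix contradictory thresholds.** This also stands. A reader might infer that the two sections set different significance levels for the same test, or that no primary contrast will be tested at 0.05. The analysis section gives no level, procedure or family, and under Benjamini-Hochberg the largest p-value is compared with 0.05 itself. Those details may properly sit in an analysis plan that is not shown. Within-group comparisons are also listed, so the family may be neither 4 nor 12.

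**More than 1260 may be available at the immediate post-test.** That survey falls on the day training ends. If nobody had withdrawn by then and clustering adds almost nothing (the stated coefficient of variation is 0.01), the signal would be 2.996 × √(1800/1260) = 3.581. Power would then be Φ(3.581 − 2.498) = 0.86 at 0.05/4 and Φ(3.581 − 2.865) = 0.76 at 0.05/12. The loss is thus not uniform across visits, and the upper bound applies to 1260 per arm. Even so, correction still costs power: uncorrected, the same test would have Φ(3.581 − 1.960) = 0.95.

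**Conclusion.** The point holds in a limited form. At the planned 1260 per arm, 0.85 is the power of a single uncorrected test and an upper bound for the corrected ones. The shortfall cannot be given as one number. On the assumptions used here it runs from about 2 points (all contrasts real, independent) to about 30 points (one real contrast among twelve).

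The assumptions are that the 0.85 is right as stated, that tests are two-sided, that Benjamini-Hochberg is used at 0.05, that the family is 4 or 12 between-group contrasts, and that all real effects have the design size. The direction does not depend on the family. It would fail only if the error rate were set above 0.05, or if the procedure estimated the share of true nulls and relaxed its threshold accordingly; the article indicates neither.

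This is a missing qualification on a stated property of the design. It is not a calculation error or a reason to doubt the planned correction. Whether the 0.85 can be derived from the inputs given is a separate issue and is not decided here.

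**What to change.** In the Sample size calculation, label 0.85 as per-test power before multiplicity correction. Then add the power of the corrected tests at 1260 per arm as a range, stating the assumed family and procedure and showing the all-effects case beside the single-effect case. For example:

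> The power of 0.85 applies to a single comparison at two-sided 0.05 before multiplicity correction. Assuming Benjamini-Hochberg at 0.05 and 1260 per arm, power per comparison is about 0.81 to 0.83 in a family of 4 (0.79 to 0.83 in a family of 12) if all comparisons have the design effect, 0.72 to 0.76 if half do, and 0.69 to 0.70 (0.55 to 0.56) if only one does.

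If the analysis plan defines another family or procedure, the range should be recomputed for it. The cost is one or two sentences and a less favourable stated power. Enrolment is unchanged; the Trial status section reports that recruitment ended by March 2023, so this is a matter of disclosure. The same wording can be carried into the results report, where it will help readers weigh a null result on a single outcome.
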